### Size of the study and power considerations

Fifty-one YHC teams of ten Youth Health Care providers participate in the study. They invited 3570 parents/children to participate in the study (two intervention groups and one control condition). Taking into account informed consent by 50% and dropout between baseline and follow-up of 30%, we expect complete data of 1250 parents/children at follow-up, equally divided over the two intervention groups and the control group. We assume equal standard deviations in the intervention groups and the control group, an alpha of 0.05 (2-tailed) and power of 0.80. We apply a correction factor to account for the cluster design, assuming an average cluster size of 25 toddlers (1250/51) and an intra-class correlation coefficient of 0.10. For this expected sample size and assumptions, we calculated minimal detectable differences between the intervention groups and the control group at follow-up.

Some illustrations: Regarding the mean number of the reported minutes of playing outside of the children per day, the study can detect a difference between an intervention group and the control group of 15 minutes/day (SD=52 min/day). Regarding the mean consumption of sweet drinks in glasses per day, a difference of 0.4 glasses/day (SD=1.5 glasses/day) can be detected. Regarding the mean number of minutes of TV viewing per day, a difference of 9 minutes/day can be detected (SD=32 minutes/day). BMI at age 36 months old: a difference of 0.38 BMI points between the mean BMI in an intervention group and the mean BMI in the control group can be detected by the study (SD=1.3).

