**Figure 1 F1:**
[figure not shown]
Flowchart of the design of the study.

Managers of all regional Youth Health Care (YHC) organizations in the Netherlands (n=50) were informed about the study and were invited to participate in the study. Ten YHC organizations volunteered to participate. In total, 51 YHC teams were available to participate in the study (three times seventeen teams). These teams covered both rural and urban regions in the Netherlands. Prior to the start of the study, the researchers arranged meetings to explain the procedure of the study, and to instruct the participating YHC professionals. Within each organization, YHC teams were randomly assigned to either one of the two intervention groups or the control group by a computerized random allocation generator. Data collection started in 2008 and continues until fall 2013.

The Medical Ethical Committee of Erasmus Medical Center has declared that the Medical research Involving Human Subjects Act (also known by the Dutch acronym WMO) does not apply to this study. The Medical Ethical Committee had no objection against the execution of this research proposal (reference number MEC-2008-250).

The study includes parents and their babies/toddlers that belong to one of the participating YHC teams, and who are eligible for the regular YHC visits from birth until age three years. The parents are informed about the study when the YHC nurse visits the parents in the second week after birth. Parents are provided with information about the study, an informed consent form, and a short questionnaire with items on background data (i.e. the baseline questionnaire); the parents were invited to provide written informed consent to participate in the study, and to complete the short questionnaire. The study design and participant flow are shown in Figure 1.

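### The stated detectable differences do not follow from the stated three-group assumptions; they fit 625 children per group rather than 417, and power at those differences is about 55–63%, not 80%

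*Protocol article*

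**What the plan says.** All inputs are in the protocol article under Size of the study and power considerations. The 3570 invitations are reduced for consent and dropout ("Taking into account informed consent by 50% and dropout between baseline and follow-up of 30" percent), after which "we expect complete data of 1250 parents/children at follow-up, equally divided over the two intervention groups and the control group". The calculation uses "an alpha of 0.05 (2-tailed) and power of 0.80", and it corrects for clustering by "assuming an average cluster size of 25 toddlers (1250/51) and an intra-class correlation coefficient of 0.10". Study design, procedure and participants agrees on three groups: "51 YHC teams were available to participate in the study (three times seventeen teams").

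The section then says that minimal detectable differences between the intervention groups and control were calculated for this sample size and these assumptions, and gives four illustrations:

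- Outdoor play: "a difference between an intervention group and the control group of 15 minutes/day (SD=52 min/day").
- Sweet drinks: 0.4 glasses/day (SD 1.5).
- Television: 9 min/day (SD 32).
- BMI at 36 months: "a difference of 0.38 BMI points between the mean BMI in an intervention group and the mean BMI in the control group" (SD 1.3).

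**The concern.** Dividing each stated difference by its SD gives 0.288, 0.267, 0.281 and 0.292 SD. These are small for a pairwise comparison of about 417 children per group with a design effect above 3, so the figures needed checking against their own inputs.

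All four illustrations concern primary outcomes, and the Discussion counts the size of the study among its strengths. If the figures are too small, readers are told that the trial is more sensitive than its design allows. A null result could then be taken as good evidence against an effect of, say, 0.38 BMI points. Anyone planning a later trial from these figures would inherit the error.

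**Working it through.** **Inputs (protocol article, Size of the study and power considerations).** Analysable children: 3570 × 0.5 × 0.7 = 1249.5, so 1250 is already net of consent and dropout. Three equal groups: 1250/3 = 416.7. Cluster size m = 25, ICC = 0.10, two-sided alpha 0.05, power 0.80. SDs: 52, 1.5, 32 and 1.3.

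**Formulas.**
- Design effect: DE = 1 + (m − 1) × ICC = 1 + 24 × 0.10 = 3.4
- Detectable difference: MDD = (1.960 + 0.842) × SD × √(2 × DE / n)
- Power at a difference d: Φ( d / (SD × √(2 × DE / n)) − 1.96 )

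**Attempt to reproduce the stated figures as planned.** With n = 416.7, the effective size is 416.7/3.4 = 122.5 per group. Then √(2/122.5) = 0.1277, and MDD = 2.802 × 0.1277 = 0.358 SD. The stated figures do not come back.

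**Same formula with 1250/2 = 625 per group.** Effective size is 625/3.4 = 183.8, √(2/183.8) = 0.1043 and MDD = 0.292 SD. This rounds to all four printed figures.

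| Outcome | Stated | 625 per group | 416.7 per group (as planned) | Planned MDD relative to stated | Power at stated difference, as planned |
|---|---|---|---|---|---|
| Outdoor play, min/day | 15 | 15.2 | 18.6 | +24% | 62% |
| Sweet drinks, glasses/day | 0.4 | 0.44 | 0.54 | +34% | 55% |
| Television, min/day | 9 | 9.35 | 11.5 | +27% | 60% |
| BMI points | 0.38 | 0.380 | 0.465 | +22% | 63% |

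Power for BMI, worked through: 0.38 / (1.3 × 0.1277) − 1.96 = 2.288 − 1.96 = 0.328, and Φ(0.328) = 0.629.

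**Other readings tried.**

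| Reading | Outdoor play | Sweet drinks | Television | BMI | Result |
|---|---|---|---|---|---|
| Three groups, m = 24.5 (DE 3.35) | 18.5 | 0.53 | 11.4 | 0.462 | No match; power 56–64% |
| Both interventions pooled against control (833 vs 417) | 16.1 | 0.47 | 9.9 | 0.403 | No match; the text compares one intervention with control |
| Three groups, one-sided alpha | 16.5 | 0.48 | 10.2 | 0.413 | No match; the text says two-tailed |
| Three groups, N before dropout (1785) | 15.6 | 0.45 | 9.6 | 0.389 | No match; the text uses 1250 |
| Three groups, ICC 0.05 (DE 2.2) | 15.0 | 0.43 | 9.2 | 0.374 | Close, but BMI rounds to 0.37; the text says 0.10 |

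**Rounding.** Taking the stated differences at their upper rounding limits (15.5, 0.45, 9.5, 0.385), power with three groups is still only 64–65%. Letting the SDs vary within their rounding as well, the highest value for any outcome is 68%.

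**Few clusters.** The plan does not specify a t reference distribution. With 17 + 17 − 2 = 32 degrees of freedom, the detectable differences rise slightly to 19.2, 0.55, 11.8 and 0.48, and power at the stated differences is 53–60%.

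**The case against.** Five points can be made for the plan.

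- **The cause is inferred.** The article never says that 1250 was halved, and an ICC near 0.053 with three groups also gives 0.38 for BMI. This stands. The halved total is the better explanation because it keeps every other stated input and rounds to all four figures. On either explanation, though, the printed results contradict the printed assumptions.
- **The 55% partly reflects rounding.** If the unrounded differences were all 0.292 SD, power with three groups would be about 63% for every outcome; 55% arises from taking 0.4 glasses as exact. This is fair: 63%, from the BMI figure given to two decimals, is the cleanest single value. It is still well below 80%.
- **Actual power could be higher.** Teams were randomised within organisations, and Data analyses plans adjustment for baseline values and confounders, so residual variance may be lower. The sample size section claims no such gain. Reaching 80% at the stated differences would need a variance reduction of about 33% (BMI) to 44% (sweet drinks). For outdoor play, television and sweet drinks, a child of 2 to 4 weeks at inclusion offers no obvious baseline equivalent. The figures here are therefore power under the stated assumptions, not a forecast of achieved power.
- **The differences are only illustrations.** They are not targets from which enrolment was derived, and randomisation, outcomes and analysis are untouched. That is true, but they are the only statement of what the trial can detect.
- **A careful reader would rely on confidence intervals.** That limits the harm but does not make the figures right.

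**Conclusion.** The concern holds. With the article's own inputs the detectable differences are 18.6 min/day, 0.54 glasses/day, 11.5 min/day and 0.465 BMI points, so the stated values are too small for all four outcomes. Power at the stated values is about 55–63%. For 0.38 BMI points the chance of missing a true effect is about 37%, against the 20% implied.

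This rests on the stated ICC of 0.10, cluster size 25, 1250 children in three equal groups, an unadjusted pairwise comparison and the normal approximation. The discrepancy itself is certain from the text. Its attribution to 625 per group is probable. The correction must be made, because the article's sole power statement is wrong on its own terms and in the optimistic direction.

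**What to change.** In Size of the study and power considerations, do one of the following:

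1. Restate the detectable differences for about 417 children per group at ICC 0.10: about 19 min/day of outdoor play, 0.54 glasses/day of sweet drinks, 11.5 min/day of television and 0.47 BMI points.
2. Keep the present differences and report power at the stated assumptions of about 55–63%.
3. If an ICC of about 0.05 was intended, state it, give its basis, and show the results for both 0.05 and 0.10.

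In each case, state the number of children per group used in the calculation. If a gain from baseline adjustment is to be claimed, give the assumed variance reduction.

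The cost is a text correction. The stated sensitivity becomes less favourable; no participants, teams or analyses change.

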### Data analyses

To assess the effect of both interventions, multilevel analyses will be applied to allow for dependency between the individual measurements within the YHC teams [30]. Multilevel linear and logistic regression analyses will be conducted for the continuous outcome variables with experimental group (i.e., intervention or control) as independent variable, and baseline values and relevant potential confounders, if any, as covariates. Multilevel logistic regression will be performed for dichotomous outcome variables. Additionally, by introducing an interaction term into the regression analyses, effect modification by gender, parental educational level, parent ethnic background, and parental overweight status will be explored. If any of these interaction terms reach statistical significance, stratified analyses will be performed.

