Secondary outcome measures are attitudes and other cognitive determinants of the parents regarding the health behaviors of their child, parenting styles and practices, and child health-related quality of life: (1) Attitudes, motivation and perceived control among parents regarding the four energy balance-related behaviors [24], (2) General parenting styles and parental practices and rules (these will be measured by Child rearing questionnaire for parents [26] and parenting practices and rules in relation to physical activity and food [27]), (3) Child health-related quality of life and wellbeing (Infant Toddler Quality of Life questionnaire - ITQOL) [24]). Concerning the secondary outcomes it is hypothesized that more favorable attitudes and other determinants of the parents regarding the overweight-related behaviors of their child will be present in each intervention group, compared to the control group. It is hypothesized that general parenting styles are less often restrictive and permissive, and more often authoritative in each intervention group compared to the control group, and that parenting practices and rules in relation to physical activity and food are more favorable in each intervention group, compared to the control group. It is hypothesized that child health-related quality of life and well-being are more favorable in each intervention group, compared to the control group.

We will explore whether one or more of the following variables have an effect on the relationship of interest, and if so, include them in the analyses as confounder: (1) Pregnancy duration and birth weight (from YHC files), (2) Parents’ BMI using self-report (self-report of adult height and weight has proven to be sufficiently accurate for epidemiological research [28]), (3) Parents’ health-related quality of life and wellbeing (SF-12), (4) Age, educational level and ethnic background of the parents.

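### Teams were randomised within ten organisations, but the stated multilevel model has only a team level; if organisations differ and arms are balanced within them, the analysis is conservative and loses power

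*Protocol article*

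**What the plan says.** On the design, the section on study design, procedure and participants states: "Within each organization, YHC teams were randomly assigned to either one of the two intervention groups or the control group". Organisation is therefore a randomisation stratum. The same section reports that "51 YHC teams were available to participate in the study (three times seventeen teams"), and the section on study size confirms the number of strata: "Fifty-one YHC teams of ten Youth Health Care providers participate in the study".

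On the analysis, the Data analyses section gives the purpose of the model: "multilevel analyses will be applied to allow for dependency between the individual measurements within the YHC teams". The predictors are experimental group together with "baseline values and relevant potential confounders, if any, as covariates". The Measurements section says how confounders will be chosen ("We will explore whether one or more of the following variables have an effect on the relationship of interest") and then lists them: pregnancy duration and birth weight, parental BMI, parental health-related quality of life, and parental age, education and ethnic background. All are characteristics of the child or the parents. Organisation does not appear as a level, a factor or a candidate covariate.

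**The concern.** Allocating teams within organisations removes differences between organisations from the comparison of arms, to the extent that each organisation contributes evenly to the three arms. A model with a random intercept for team only cannot use this. It counts organisation differences as team differences, and the team variance is what sets the standard error of the arm contrast. Precision bought by the design is then not credited in the analysis: confidence intervals are wider than they need to be and the test runs below its nominal 5%. With 17 teams per arm there is little precision to spare.

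**Working it through.** **Inputs from the article.** 51 teams, 17 per arm, ten organisations; 1250 children at follow-up, so 1250/3 = 416.7 per arm; "an alpha of 0.05 (2-tailed) and power of 0.80"; and "assuming an average cluster size of 25 toddlers (1250/51) and an intra-class correlation coefficient of 0.10".

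**Assumed.** The organisation part of the 0.10, written v, is not given. I use v = 0, 0.02, 0.05 and 0.08. Team numbers per organisation are not given either; I take nine organisations with 5 teams and one with 6.

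**The plan's own figure.** The design effect is 1 + 24 × 0.10 = 3.4, so the effective size is 416.7/3.4 = about 122 per arm. The detectable difference is (1.96 + 0.84) × √(3.4 × 2/416.7) = 0.358 SD, or 0.358 × 1.3 = 0.465 BMI points. The article states 0.38 BMI points, which these inputs do not reproduce. That is a separate matter and does not affect this point. I use 0.358 SD as the reference effect because it has a nominal 80% power under the article's own inputs.

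**Upper limit, perfect balance within organisation** (SD units, variance of one arm contrast):

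- team-only model: 2 × (0.10/17 + 0.9/416.7), so SE = 0.1268 whatever v is;
- true variance: 2 × ((0.10 − v)/17 + 0.9/416.7), so SE = 0.1172, 0.1010 and 0.0817 at v = 0.02, 0.05 and 0.08;
- ratios: 1.08, 1.26 and 1.55.

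About five teams cannot be split evenly over three arms, so these ratios are a ceiling.

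**Near-balanced allocation.** I simulated 17 teams per arm, spread as evenly as possible within each organisation, and analysed team means by t-test without and with organisation as a fixed factor (6000 runs per setting):

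| v | Team-only SE too large by | Type I error, team only | Power at 0.358 SD, without / with organisation |
|---|---|---|---|
| 0 | about 0% | about 5% | 80% / 77–78% |
| 0.02 | 4% | 4.1% | 80% / 83% |
| 0.05 | 16% | 2.2% | 83% / 93% |
| 0.08 | 35% | 1.0% | 86% / 99% |

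With organisation in the model, type I error stayed at 4.9% to 5.3%. A repeat with 20,000 runs gave inflation of 6%, 18% and 37% at v = 0.02, 0.05 and 0.08, and power within about one point of the table. The inflation figures are therefore good to two or three percentage points.

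**No balance within organisation.** When the 51 teams were allocated 17/17/17 without regard to organisation (5000 runs), the ratio of team-only SE to true SD was 1.01 to 1.02 and type I error 4.6% to 5.0%. The team-only SE is then about valid. Adjustment changed the SE from 0.1265 to 0.1407 at v = 0, from 0.1260 to 0.1275 at v = 0.025, from 0.1246 to 0.1116 at v = 0.05, and from 0.1236 to 0.0942 at v = 0.075.

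All of this is for continuous outcomes and ignores child-level covariates.

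**The case against.** This is a journal article that condenses a fuller plan, and stratification terms are often left to the analysis plan. The article does name the unit of randomisation as the clustering level, which is correct, and it does not say that organisation is excluded. That has some weight, but the topic is not left open: the article states the level of dependency, the predictors and the list of candidate covariates, and what it states does not match the randomisation that it describes.

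A reader might infer that the standard errors simply are too large. The documents do not support this. It needs organisations that differ, and no between-organisation variance is given; it also needs arms balanced within organisations, and the article mentions only a computerised generator and 17 teams per arm overall. An exact 17/17/17 split has a probability of 51!/(17!)³/3⁵¹ = 1.6% under simple randomisation, so some restriction is likely, but that does not show balance inside each organisation. The parental covariates may also absorb some of the differences between organisations.

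A reader might also take the perfect-balance ratios (8%, 26% and 55%) as the size of the problem, or compare the nominal detectable difference of 0.355 SD with 0.28 SD after adjustment at v = 0.05. Both overstate it. The ratios need a balance that is not attainable with about five teams per organisation. The second comparison uses the nominal SE, whereas under the same formula the team-only test already reaches 80% power at 1.96 × 0.1268 + 0.84 × 0.1010 = 0.333 SD.

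Finally, the error is in the safe direction: it is a loss of efficiency and not a threat to validity.

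**Conclusion.** The point stands in conditional form. The stated model omits the stratum within which teams were randomised. If organisations differ and arms are roughly balanced within them, the test is conservative. The size rests on the assumed split of the 0.10 and on the assumed five or six teams per organisation. At v = 0.02 the loss is small, about 3 points of power. At 0.05 it is about 10 points and at 0.08 about 13. If v is zero nothing is gained, and under near-balance adjusting loses 2 to 3 points. The teams cover rural and urban regions, so some difference between organisations is plausible. The change is worth making, but the documents do not show how much it will gain.

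**What to change.** Add organisation (10 strata) as a fixed factor to every multilevel linear and logistic model, and keep YHC team as the random level. Where a sparse binary outcome prevents convergence, use organisation as a higher random level for that outcome only; ten units are few for estimating a variance, so this should stay the exception. State this before outcome data are analysed by arm, and report the number of teams per arm within each organisation so that readers can see the balance achieved.

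The cost is one sentence in the plan and 9 degrees of freedom out of 51 teams; the organisation of every team is already known. The less favourable case is arms poorly balanced within organisations that hardly differ: in the simulation without balance at v = 0, adjustment raised the SE by 11% (0.1407/0.1265).

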## Discussion

In this paper the study protocol of a cluster randomized controlled trial regarding primary prevention of overweight and obesity in preschool children has been presented. The study will evaluate two overweight prevention interventions, of which the ‘BBOFT+’ intervention starts immediately after birth and the ‘E-health4Uth’ intervention starts at the age of circa 18 months. The interventions are offered by preventive Youth Health Care (YHC) centers in addition to the currently applied overweight prevention protocol for parents of preschool children in the Netherlands.

It is hypothesized that positive effects on various aspects of child lifestyles and BMI will be demonstrated among children in the two intervention groups in comparison to children in the control group. Several process characteristics including adherence and satisfaction by both parents and professionals will also be analyzed. This will provide insights relevant for future implementation, when the interventions prove to be successful.

Strengths of the study are the size of the study, and the randomizations of YHC teams (c-RCT design). Because the last measurement will be at child age 36 months, it will be possible to also investigate medium-term effects of the interventions (circa 1 year follow-up after the last E-health4Uth Healthy Toddler intervention). Another strength will be that the study is conducted in the setting of daily YHC practice, which will facilitate future implementation if the interventions are found to be effective. The participating YHC teams cover urban as well as rural areas, which will support generalization of the findings. A limitation of the study will be that the behaviors of the children and their parents are based on self-report by the parents.

In conclusion, this study will evaluate a protocol for the prevention of overweight and obesity in preschool children. The results of this study will provide insight into the effectiveness of two interventions that may be applied in child public health in the Netherlands.
